### Sample size

Considering a difference in peak oxygen intake of 2.9 ml.kg^−1^.min^−1^ with a standard deviation of 2.0 ml.kg^−1^.min^−1^ [38], assuming an *α* = 0.05 and *β* = 0.20, and increasing the sample size by 50 % accounting for losses to follow-up, a total of 30 patients (15 in the control group and 15 in the exercise group) will be included.

### Randomization

A sequence will be computer-generated to randomly allocate 30 patients into two groups in a 1:1 ratio (WinPepi version 11). The sequence will be generated in blocks and by strata of CHD classification (B2 and C) by a single researcher not involved in recruitment. Opaque envelopes will be filled in sequentially to either control or exercise group. Block size will be blinded from investigators involved in patients’ recruitment.

### Blinding

Given that exercise implies a behavioral intervention, it is not feasible to blind the patients. However, the evaluators will be blinded to the primary endpoint obtained by the CPET and the following secondary endpoints: microvascular reactivity, cardiac rhythm abnormalities, cardiovascular autonomic function test, and laboratorial biomarkers. A blinded researcher will perform all data analysis.

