However, exercise studies including patients with Chagas disease are warranted since these patients are usually not included in exercise clinical trials [10]. The first study that addressed the effects of exercise training on CHD showed that functional capacity, clinical symptoms, and some domains of health-related quality of life (vitality, emotional aspects, and mental health) improved after 3 months of follow-up [11]. Another single-arm study demonstrated that oxygen consumption at peak of exercise (VO_2_ peak), oxygen pulse (O_2_ pulse), and oxygen consumption at anaerobic threshold (VO_2_ AT) improved after 6 months of exercise training [12]. However, the interpretation of these results is limited by the short-term follow-up in the former study and the lack of a control group in the later study. Thus, new well-designed clinical trials are necessary to improve the knowledge of CR effects on patients with CHD.

The PEACH study, which stands for “Exercise Program in Chagas Heart Disease” in Portuguese, is designed to address the effects of exercise training in patients with CHD. The primary aim of the study is to investigate the effects of exercise on functional capacity in patients with CHD, measured as the VO_2_ peak during a maximal progressive cardiopulmonary exercise test (CPET). Secondary objectives are to assess the effects of exercise training on cardiac function, body composition, muscle respiratory strength, microvascular reactivity, cardiac rhythm abnormalities, autonomic function, biochemical, inflammatory and oxidative stress biomarkers, and quality of life. We hypothesized that exercise training will be safe and will promote important clinical benefits mainly on functional capacity among patients with CHD.

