### Participants and recruitment

Individuals followed at INI will be sequentially recruited to participate in the study. The eligibility criteria are: (1) Chagas disease diagnosis, confirmed by two simultaneous serological tests (enzyme-linked immunosorbent assay (ELISA) and indirect immunofluorescence) [3], (2) CHD with LVEF <45 % with or without HF symptoms at baseline evaluation (CHD stages B2 and C), (3) New York Heart Association class I or II in the previous 3 months, with clinical stability by investigator judgment, (4) clinical treatment according to HF guidelines, including treatment with angiotensin-converting enzyme inhibitors or angiotensin receptor blockers, and beta-blocker therapy, or documented rationale for variation, including intolerance, contraindication, or patient preference [13, 14]. Patients will be on stable doses of medications for 6 weeks prior to enrollment, and (5) age above 18 years. Exclusion criteria are: (1) pregnancy, (2) neuromuscular limitations that preclude physical exercise, (3) smoking, (4) evidence of known non-chagasic heart disease, (5) systemic conditions that limit exercise practice or CPET, (6) unavailability to attend the center three times a week during the intervention period, and (7) practitioners of regular exercise.

Trained research assistants or study investigators will conduct the evaluations in a quiet and private room. Initial interviews will include a questionnaire to collect sociodemographic data (income, race, age, sex, and schooling), medical history (stage of CHD, comorbidities, medication, cardiac devices, and arrhythmias), functional class, and level of physical activity through the International Physical Activity Questionnaire-Short Form (IPAQ-SF). Evaluations of functional capacity (maximal progressive CPET), cardiac function (two-dimensional echocardiography), body composition (anthropometry and skinfolds), muscle respiratory strength (manovacuometry), microvascular reactivity (laser speckle flowmetry), cardiac rhythm abnormalities (24-h Holter), autonomic function (active orthostatic stress test), laboratorial biomarkers (biochemical, inflammatory, and oxidative stress), and quality of life (Short Form-36 (SF36) and Minnesota Living with Heart Failure Questionnaire) will be performed at baseline, after 3 months, and at the end of follow-up (6 months). After initial evaluation, patients will be randomized to intervention or control groups as seen in Fig. 1.

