#### Respiratory muscle strength

Respiratory muscle strength will be assessed by maximal inspiratory (MIP) and expiratory pressures (MEP) using a digital pressure manometer connected to a mouthpiece (MVD 3000®, Globalmed, Brazil). Patients will remain in a seated position with a nose clip. They will be requested to make a maximum inspiratory effort at residual volume and a maximum expiratory effort at total lung capacity, sustaining it for 1 to 2 s [26]. Once the operator is satisfied, the maximum value of three maneuvers that vary by less than 20 % will be recorded [27].

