In the PEACH study, we will try to fill this knowledge gap and address the issue of whether patients with CHD have the same benefits promoted by exercise training in patients with cardiomyopathies from other etiologies. We hypothesize that exercise training will be safe and promote improvements in functional capacity and quality of life, as previously demonstrated by Lima et al. [11] and Fialho et al. [12] in a different sample of patients with CHD. Since an exacerbated inflammatory response is an important mechanism involved in the development of CHD [46] and because several studies have been demonstrating an important anti-inflammatory property of exercise training [47], a decrease in the serum levels of pro-inflammatory cytokines and an increase in the serum levels of anti-inflammatory cytokines in patients with CHD in the exercise group is expected. Although enhancements in autonomic function as results of exercise training are present in studies with other cardiomyopathies [48], a recent article did not confirm this finding in patients with CHD [30]. We also hypothesize that cardiac function will improve by an increase in LVEF and an improvement in diastolic function, as seen in coronary artery disease [49], and that exercise will improve body composition, respiratory strength, microvascular reactivity, and oxidative stress agents based on results from studies evaluating exercise in non-CHD patients [50, 51].

The benefits of exercise training that will be described by this study will set a new treatment strategy for CHD patients and that this strategy could be routinely included in clinical practice.

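### The assessor-blinding list leaves out echocardiography, respiratory muscle strength and skinfolds, so these secondary outcomes carry an avoidable risk of observer bias

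*Protocol article*

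**What the plan says.** The Blinding section of the protocol article first accepts that, with an exercise intervention, "it is not feasible to blind the patients". It then names the outcomes that have blinded evaluators: "the evaluators will be blinded to the primary endpoint obtained by the CPET and the following secondary endpoints: microvascular reactivity, cardiac rhythm abnormalities", and the sentence ends with "cardiovascular autonomic function test, and laboratorial biomarkers". The same section adds: "A blinded researcher will perform all data analysis".

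The set of secondary outcomes is wider than that list. The Background states: "Secondary objectives are to assess the effects of exercise training on cardiac function, body composition, muscle respiratory strength, microvascular reactivity, cardiac rhythm abnormalities, autonomic function", and goes on to biomarkers and quality of life. On who does the measuring, Participants and recruitment says: "Trained research assistants or study investigators will conduct the evaluations in a quiet and private room". It mentions no blinding.

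The method sections for the three unlisted outcomes are as follows.

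- **Cardiac function:** LVEF is estimated by the biplane Simpson's method. No blinded reader is named.
- **Body composition:** seven skinfold sites are measured by caliper, each twice and then averaged. No blinded assessor is named.
- **Respiratory muscle strength:** the recording rule begins "Once the operator is satisfied, the maximum value of three maneuvers" and also requires the three to agree within 20 %. No blinded assessor is named.

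The Discussion states the expected direction: "We also hypothesize that cardiac function will improve by an increase in LVEF". The same sentence predicts better body composition and respiratory strength.

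**The concern.** The one reason given for limited blinding is that patients know whether they are exercising. That does not explain why whoever reads an echocardiogram, applies a caliper or runs a MIP/MEP session should know the arm. The protocol keeps the arm from the CPET evaluator, who also tests the patient face to face.

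The three unlisted outcomes leave some room for judgement or encouragement, and the investigators have recorded which way they expect them to move. If an assessor knows the arm and shares that expectation, part of any reported gain in LVEF, respiratory strength or body composition could come from the measuring. The Discussion intends the described benefits to support a new treatment strategy, so positive secondary results would be put to use.

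**Working it through.** The plan gives no figure on this point, so the check compares the outcome list with the blinding list and then traces where a biased reading would go.

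**Step 1: outcomes against the blinding list.** Sources are the Background, the individual outcome sections and the Blinding section.

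| Outcome domain | Blinded evaluator stated? |
|---|---|
| CPET (primary: peak VO2) | Yes, in Blinding and again in the CPET section |
| Microvascular reactivity | Yes |
| Cardiac rhythm (Holter) | Yes |
| Autonomic function test | Yes |
| Laboratory biomarkers | Yes |
| Cardiac function (echocardiography) | No |
| Body composition (skinfolds) | No |
| Respiratory muscle strength (MIP/MEP) | No |
| Quality of life | No |

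Five of nine domains are covered and four are not. Quality of life is reported by patients who know their group, so assessor blinding would not cure it, and it is set aside. The other three are the point at issue. I take blinding *to* an endpoint, as the section words it, to mean blinding to allocation when that endpoint is measured.

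**Step 2: is the list closed?** It is introduced as the secondary endpoints that follow, and it ends without any catch-all. The outcome sections agree with it: the CPET section names a blinded evaluator, and the three sections above do not. The article therefore states a selective rule. This is not a detail left to a fuller document.

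**Step 3: where a biased reading would go.** Participants and recruitment places randomization after the initial evaluation, so the arm cannot influence a baseline reading taken at that evaluation. It can influence readings at 3 and 6 months. Let *b* be the difference between arms in any expectation-driven shift, equal at both follow-up visits. The spurious between-arm differences at 0, 3 and 6 months are then 0, *b* and *b*.

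- With time as visits, the estimated effect is the true effect plus *b* at each follow-up visit.
- With time linear and complete data, the mean time is 3 months and the spurious slope is [(−3)(0) + (0)(*b*) + (3)(*b*)] / [9 + 0 + 9] = 3*b*/18 = *b*/6 per month. Over 6 months this is again *b*.

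Either way the whole shift enters the treatment × time interaction that the Statistical analysis section uses to judge the outcomes. The mixed model cannot separate it from a treatment effect. A blinded analyst cannot remove it, because it is already in the data.

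**Step 4: what the repeat-measurement rules do.** Averaging two caliper readings reduces random error, and the 20 % agreement rule limits erratic efforts. Neither acts on a shift common to all readings in a session: if every reading moves by *b*, their average and their maximum also move by *b*.

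**Step 5: size.** The documents contain nothing from which *b* could be estimated.

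**The case against.** The strongest reply is that the plan protects what matters most and is open about the rest. The primary outcome, a symptom-limited test that an examiner may interrupt, has a blinded evaluator. So does the autonomic test, which includes blood pressure readings timed to within seconds of standing. Blinding is therefore not reserved for instrument-read measures. All data analysis is blinded, skinfolds are taken in duplicate, and MIP/MEP uses a digital manometer with a numerical agreement rule. In a single-centre trial of 30 patients, staffing may be the real constraint.

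Most of this stands, and it narrows the point to three secondary outcomes. It does not answer it: analyst blinding acts after measurement, the repeat rules act on random error, and no staffing reason is given.

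A reader might infer more than the documents support.

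- *That these assessors will know the arm.* The article gives no assurance that they will not, but it does not say that they will.
- *That these are the most operator-dependent outcomes, with LVEF traced by hand and MIP/MEP efforts coached.* The article ranks nothing, does not say how the Simpson estimate is produced, and says only that patients are requested to make maximal efforts.
- *That cardiac function ranks first among the secondary outcomes.* It is listed first, but no order of importance is stated.
- *That the bias can be sized from the sample size.* For a single-visit comparison with SD *s*, the standard error is *s*√(2/15) = 0.365*s* with 15 per arm, or *s*√(2/10) = 0.447*s* with, for example, 10 completers per arm. This measures precision and says nothing about how large a reader's shift would be. It is also not the standard error of the planned mixed model.

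**Conclusion.** The concern holds as a limited one. The Blinding section leaves echocardiography, MIP/MEP and skinfolds outside assessor blinding without giving a reason, although they depend partly on the operator and the Discussion states directional hypotheses for them. Any arm-related expectation effect at 3 or 6 months would pass in full into the estimated effect on these outcomes.

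This is a risk of bias, not a demonstrated bias, and its size cannot be derived from the document. It does not touch the primary peak VO2 comparison. Nor does it follow that gains in LVEF, strength or body composition would be artefacts, only that the plan as written does not exclude that explanation.

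The conclusion assumes that the list is complete as printed and that the omitted assessors could learn the allocation. If they are in fact blinded, only the wording of the Blinding section needs correcting.

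**What to change.** Extend the list in the Blinding section to echocardiography, respiratory muscle strength and skinfold body composition:

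- withhold the arm from the existing echocardiography reader;
- have existing staff not involved in training, for example the evaluator already blinded for CPET, take MIP/MEP and skinfolds;
- ask patients not to disclose their group to assessors.

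Where staffing does not allow this for an outcome, say so, report that outcome as assessed unblinded, and interpret it accordingly. The Trial status section says recruitment is under way, so follow-up visits still to come can be protected. Any taken before the change should be identified as not covered by it.

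The cost is a change of wording and minor scheduling effort. It depends on suitable existing staff being available, which the article does not document. Some unblinding by patients will remain, and assessor blinding does not stop patients who know their group from varying their own effort on MIP/MEP.

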### Interim analysis and stopping rules

Three interim analyses are planned. The first will be conducted when the tenth volunteer completes 3 months of follow-up, the second when the twentieth volunteer completes 3 months of follow-up and the third when the last volunteer completes 3 months of follow-up.

Trial interruption for ethical reasons due to either positive or negative results exceeding expectations may be recommended by an independent committee. The pre-specified stopping rule is a difference of 50 % in VO_2_ peak between groups, serious adverse events twice as frequent in one of the groups as cardiovascular death, acute myocardial infarction, unstable angina, cardiopulmonary arrest, malignant ventricular arrhythmias, decompensated HF, and stroke. All these estimates should have a significance level of 0.01 or less in any of the interim analyses.

### Statistical analysis

Descriptive analysis will consist of mean and standard deviation for continuous variables and percentage for categorical variables. Skewness and Kurtosis testing will be performed to assess the normality of data which will be log-transformed in case of skewed distribution. Variables that can change prognosis of the disease will be compared at baseline in relation to the exercise and control groups. Longitudinal effects of exercise on primary and secondary outcomes will be evaluated through linear mixed models (LMM), which correlate with repeated measures over the time. LMM is an intention-to-treat analysis as it includes all observations of each one of the patients regardless of losses to follow-up or noncompliance to exercise protocol. The longitudinal analysis will be made by the treatment × time interaction, which estimates the rate of changes in the outcomes. Residual plots of all models will be examined and the likelihood-ratio test will be used to compare and select random intercept or random slope models.

The REDCap software will be used for data management and the data analysis will be conducted by Stata 13.0 software. Statistical significance will be set at *p* < 0.05 for all analyses.

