#### Cardiopulmonary exercise test

The primary outcome is functional-capacity-based on VO_2_ peak obtained by a CPET using the VO_2000_ gas analyzer (MedGraphics®, St. Paul, MS, USA) with a computerized system Ergo PC Elite (Micromed®, Brasília, Brazil) and a treadmill (Inbramed®, Porto Alegre, Brazil). A blinded evaluator will perform an incremental exercise test using a ramp protocol, tailored to achieve a fatigue limited exercise duration of approximately 8 to 12 minutes. [18]. The workloads will be based on age, gender, height, and weight; adapted to each subject’s physical condition and effort tolerance. Gas and volume calibrations will be executed on the early morning of each test day. Pulmonary gas exchange will be analyzed breath-by-breath and averaged every 10 s. A 12-lead electrocardiogram will monitor heart rhythm during CPET.

The CPET will be limited by symptoms through the subjective fatigue perception scale (Borg modified) ranging from 0 to 10, with 0 representing absence of fatigue and 10 maximum tolerated efforts. The examiner may interrupt the test in case of identification of any harmful hemodynamic response. The recovery phase will be active with walking in a pre-determined velocity of 2 km.h^−1^ and 2 % of inclination.

The following CPET variables will be analyzed: maximum achieved heart hate (HRmax); maximum achieved blood pressure (BPmax); respiratory exchange ratio (VCO_2_/VO_2_); oxygen consumption at peak of exercise (VO_2_ peak); oxygen consumption at anaerobic threshold (VO_2_ AT); oxygen pulse (O_2_ pulse); ventilation slope equivalent to carbon dioxide production (slope VE/VCO_2_); circulatory power (CP); presence of complex ventricular arrhythmias (VA); functional aerobic impairment (FAI); and oxygen uptake efficiency slope (OUES) values.

The VO_2_ peak during exercise will be defined as the greatest value during 30 s before and after maximum effort. The VO_2_ AT will be determined by the point at which expired carbon dioxide increases in a nonlinear fashion relative to the rate of oxygen consumption according to the V-slope method. Ergo PC Elite software will determine the other variables obtained on the CPET.

Before CPET, the rest electrocardiogram will be evaluated to define if the cardiac rhythm is acceptable to perform the exam. The following markers will not be accepted: sustained ventricular tachycardia, second- and third-degree atrioventricular block, atrial or supraventricular tachycardia (more than 100 bpm).

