#### Cardiac rhythm abnormalities

Arrhythmias and heart rate variability (HRV) will be evaluated with a 24-h Holter (portable three-channel recorder and analyzer; Cardio Light® and CardioSmart® 5.0, Cardio System, São Paulo, Brazil). Patients will be requested to maintain their normal daily activities during the exam. Standard frequency- and time-domain heart rate variability indexes will be measured and evaluated in patients who do not have artificial pacing or atrial fibrillation rhythm. Only tracings of at least 18 h will be studied. Standard time-domain HRV indices (SDNN: standard deviation of normal-to-normal RR intervals; SDANN: standard deviation of the averages of normal-to-normal RR intervals in all 5-min segments of a 24-h recording; SDNNIDX: mean of the standard deviations of normal-to-normal RR intervals in all 5-min segments of a 24-h recording; rMSSD: root mean square of successive differences; and PNN >50: percentage of differences between adjacent normal-to-normal RR intervals that are greater than 50 ms) and frequency domain (TP: total power; VLFP: very low-frequency power; LFP: low-frequency power; HFP: high-frequency power) will be calculated [30–32].

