#### Quality of life

The short-form version of the SF-36 Health Survey [36] and the Minnesota Living with Heart Failure Questionnaire [37] will be used to assess quality of life, all of them previously translated and validated in Portuguese.

The SF-36 consists of 36 questions in eight different domains: general health, physical functioning, social functioning, mental health, physical role, emotional role, bodily pain, and vitality. Each of these dimensions range from 0 (worst possible health state) to 100 (best possible health state).

The Minnesota Living with Heart Failure Questionnaire has 21 questions about how the heart disease influences the lifestyle related to physical, psychological, and social areas. Each question’s responses range from 0 (none) to 5 (very much) and the maximum score is 105. In this questionnaire, lower scores mean better quality of life.

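### One Gaussian mixed model and a log-if-skewed rule are fixed for every outcome, which does not suit a yes/no arrhythmia variable or scores that can be 0, and leaves the scale of VO2 peak to a test on the data

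*Protocol article*

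**What the plan says.** Everything that governs the analysis is in the protocol article under Statistical analysis.

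- **Model.** "Longitudinal effects of exercise on primary and secondary outcomes will be evaluated through linear mixed models (LMM"). No outcome is exempted. The only model choice left open is random intercept or random slope, decided by a likelihood-ratio test.
- **Transformation.** "Skewness and Kurtosis testing will be performed to assess the normality of data which will be log-transformed in case of skewed distribution". There is no rule for zeros, none for left skew, and no exempt outcome.
- **Completeness.** "LMM is an intention-to-treat analysis as it includes all observations of each one of the patients regardless of losses to follow-up" or poor adherence to the exercise programme.
- **Checks.** "Residual plots of all models will be examined", with no stated consequence.
- **Categorical variables** appear only in the descriptive plan: "mean and standard deviation for continuous variables and percentage for categorical variables".

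The outcomes to which this applies include:

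- under Cardiopulmonary exercise test, among the variables to be analysed, "presence of complex ventricular arrhythmias (VA");
- under Quality of life, the SF-36 domains: "Each of these dimensions range from 0 (worst possible health state) to 100 (best possible health state"). The Minnesota questionnaire has 21 items scored 0 to 5, a maximum of 105, and lower scores are better;
- the primary outcome, VO2 peak. Under Sample size the trial is sized on a difference of 2.9 ml/kg/min with a standard deviation of 2.0.

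**The concern.** The article states a method here; it does not leave one open. Followed literally, the method has three consequences.

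1. **Binary variable.** A Gaussian model is fitted to a 0/1 outcome. Fitted risks can fall below 0 or above 1, and with 15 patients per arm some arm-by-visit cells may hold no events. If the skewness rule were also applied, the log would be undefined for every patient without the arrhythmia.
2. **Scores that include 0.** A score judged skewed is logged, and log(0) does not exist, so that visit leaves the model. On the Minnesota scale a 0 is the best possible result. If exercise works, more zeros are expected in the exercise arm, so the loss depends on the outcome and works against the treatment. A patient's other visits do not repair it. SF-36 domains can instead be left-skewed, with values bunched near 100, and the log then makes the skew worse.
3. **Primary outcome.** VO2 peak is not exempt. A normality test on the data could move its analysis from an additive difference to a ratio, which is a different estimand from the one used to size the trial.

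**Working it through.** **The plan's own figure.** With difference 2.9, SD 2.0, two-sided alpha 0.05 and power 0.80, the normal approximation gives 8 per arm and the t-based calculation 9 per arm (power 0.823). Then 9 × 1.5 = 13.5, rounded up to 14 per arm, or 28 in total; 8/(1 − 0.5) = 16 per arm, or 32 in total. Both are within 2 of the stated 30. The sample size is not in dispute. It matters here because it is built on an additive ml/kg/min scale.

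**Binary variable.** The article gives no event rate, so a range was simulated: 15 per arm, three visits, complete data, no treatment effect, a random-intercept linear model with a z test of treatment × time, and 10,000 runs per setting. Event probability is for the median patient; the two values in each cell are for a between-patient SD of 1 and 2 on the logit scale.

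| Assumed probability | Type I error | Fitted arm mean outside 0–1 | At least one arm-visit cell with no events |
|---|---|---|---|
| 0.05 | 0.050 / 0.051 | 29 % / 9 % | 89 % / 47 % |
| 0.10 | 0.058 / 0.057 | 9 % / 2 % | 51 % / 17 % |
| 0.20 | 0.052 / 0.057 | 1 % / 0.2 % | 10 % / 3 % |

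At 0.30 and 0.50, type I error was 0.053 to 0.059 and out-of-range fits were 0.1 % or less. The test holds its level. The fault lies in the fitted values and the sparse cells, when events are rare.

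**Zeros under the log.** There are at most 30 × 3 = 90 observations per outcome. Let q be the chance of a zero per observation (assumed; the article gives none). Expected loss is 90q. Patients losing at least one visit number 30 × (1 − (1 − q)³) if zeros are independent across visits, and 30q if they always recur in the same patients.

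| q | Observations lost | Chance of at least one (independent zeros) | Patients losing a visit |
|---|---|---|---|
| 1 % | 0.9 | 60 % | 0.3 to 0.9 |
| 5 % | 4.5 | 99 % | 1.5 to 4.3 |
| 10 % | 9 | over 99.9 % | 3 to 8.1 |
| 20 % | 18 | over 99.9 % | 6 to 14.6 |

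**Direction of that loss.** As an illustration, take Minnesota scores as normal with SD 15, rounded and floored at 0, with control mean 15, 20 or 25 and exercise 8 points lower (all assumed). Zeros are then 17 %, 10 % and 5 % in control, and 33 %, 22 % and 14 % in exercise. Removing them shrinks the raw difference in means by 29 %, 25 % and 20 %.

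**Left skew.** The log stretches the low end. Between 20 and 40 the gap becomes ln(40/20) = 0.69; between 80 and 100, the same 20 points, it becomes ln(100/80) = 0.22. A score bunched near 100 with a low tail therefore gets a longer tail.

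**VO2 peak.** With 30 values, a skewness test at 5 % is positive in about 5 % of truly normal samples. If VO2 peak were lognormal with coefficient of variation 0.20 to 0.30 (assumed), it is positive in 21 % to about 37 %. On the log scale the planned 2.9 is no longer one number: from an assumed baseline of 15 it is 2.9/15 = 19 %, and from 20 it is 2.9/20 = 14.5 %.

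**The case against.** The strongest reply is that this is a condensed article, that models by outcome type and offsets for zeros usually sit in an analysis plan, and that the article provides residual plots and a blinded analyst. That would answer a silence, but the article assigns the model to all outcomes and fixes the transformation. Residual plots carry no stated action, and blinding the analyst neither restores a logged zero nor keeps the primary estimand fixed.

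Other parts of the reply stand and limit the point.

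- **A reader might infer that binary results would be invalid or their standard errors wrong.** That is not supported. Even with events in 1/15 v 4/15 (illustrative), where the variances are 0.062 and 0.196, equal arms give the same standard error of the between-arm difference pooled, √(2 × 0.129/15) = 0.131, as unpooled, √((0.062 + 0.196)/15) = 0.131. The simulated type I error agrees.
- **A reader might infer that patients scoring 0 are dropped.** The model loses the visit, and the patient only if every visit is 0. This happens only if the score is judged skewed and zeros occur.
- **A reader might take postural hypotension as yes/no and Holter arrhythmias as counts.** The Cardiovascular autonomic function test section describes blood pressures and an RR ratio, with no cut-off. The Cardiac rhythm abnormalities section says only that "Arrhythmias and heart rate variability (HRV) will be evaluated with a 24-h Holter", and the indices it defines are heart rate variability measures. Neither coding is stated.
- The arrhythmia variable is one of eleven exercise test variables, not a separately named secondary endpoint. Serious arrhythmic events are compared under Interim analysis and stopping rules, where the mixed model is not mentioned.
- VO2 peak is strictly positive, so it loses no observations, and the article gives no evidence that it will be skewed.

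**Conclusion.** The point holds in this limited form. The stated rule does not fit one listed binary variable. It conflicts with the all-observations statement for any logged score containing a zero, it worsens left skew, and it leaves the scale of the primary analysis to a test on the data. It should be corrected, but it does not affect the sample size and has no demonstrated effect on the primary result.

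The size rests on assumptions, because the article reports no frequency of zeros, arrhythmias or skew. Over a 1 % to 20 % chance of a zero, 0.9 to 18 of 90 observations would be lost. Zeros at or near that level are plausible for the Minnesota score, since entry is limited to New York Heart Association class I or II. Out-of-range fits for the binary variable matter only at event probabilities of about 10 % or below. The chance that VO2 peak is logged runs from about 5 % if it is normal to about 37 % under the most skewed case tried.

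**What to change.** Replace the general rule under Statistical analysis with a few sentences:

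- Linear mixed models apply to continuous outcomes only.
- VO2 peak, SF-36 domains and Minnesota scores are analysed on their original scales in all cases, and fit is judged from residuals.
- Presence of complex ventricular arrhythmias, and any other outcome that turns out to be coded yes/no, is reported as counts by arm and analysed by a binary method: an exact comparison, a penalised or mixed logistic model, or GEE. The choice is named in advance.
- The log is pre-specified for strictly positive, right-skewed assays such as NT-proBNP and the cytokines, and is not triggered by a normality test.

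The cost is the wording and a few different model commands; no data collection or sample size changes. The downside is low power for rare binary events with 30 patients. A linear model does not remove that limit.
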